# Study Synopsis

The PrePex device was accepted for the World Health Organization (WHO) list of prequalified male circumcision (MC) devices and was listed on 31 May 2013.

PrePex became the first medical device for adult male circumcision to receive WHO prequalification as an alternative to the conventional surgical circumcision methods already recognized by WHO.

Voluntary Medical Male Circumcision (VMMC) is a one-time, low cost intervention that shown to reduce men’s risk of HIV infection by approximately 70 percent. The WHO recommends VMMC as part of a comprehensive package of HIV prevention services. The WHO prequalification of PrePex represents an unprecedented opportunity to further the safe and rapid scale up of voluntary medical male circumcision programs [Official statement by the Office of the U.S. Global AIDS Coordinator].

Up to date more than 7,500 MCs were performed using the PrePex device. Rwanda, Zimbabwe and Uganda have completed the WHO clinical roadmap, scientifically validating the safety, efficacy, acceptability and superiority (over dorsal slit, on both measures of time and safety) of PrePex, other countries such as Kenya, Botswana and Mozambique are currently conducting PrePex pilot studies.

A concern that was raised by WHO TAG consulting members regarding the potential acceptability of PrePex by men involved the potential of strong odor extraction from the necrotizing foreskin. PrePex researchers from Rwanda have assumed that there is a possible relation of the level of odor to the personal hygiene and foreskin washing technique. It is speculated that when a patient follows an appropriate washing technique of the foreskin while wearing the device, the odor before device removal (day 7) will be redundant and significantly lower than the odor of the foreskin of a patient that does not follow such washing instructions and technique. Providing scientific evidence of the direct relation between odor and personal hygiene will allow VMMC implementing bodies to create a comprehensive and effective PrePex personal hygiene protocol and increase acceptability of the VMMC.

This clinical study will include the following objectives:

- To compare the different odor levels when examining 3 arms with identical personal hygiene but different foreskin hygiene techniques
- To determine a detailed and validated foreskin cleaning procedure protocol, that will ensure low odor without compromising safety

To compare the different perception of the subject’s partner relating to the odor when examining 3 arms with identical personal hygiene but different foreskin hygiene techniques.

This protocol describes the endpoints and methods of assessing those objectives.

**Study Design and Title:**

Assessing Odor Level when Using PrePex for HIV Prevention: A Prospective, Randomized, Open Label, Blinded Assessor Trial to Improve Uptake of Male Circumcision.

**Planned Number of Subjects:**

At least one hundred (100) adult men scheduled to undergo VMMC.

**Study Duration:**

Study duration per subject will be up to 1 week (Placement visit and Removal visit after 7 days).

**Primary Objectives:**

- To compare the different odor levels when examine 3 arms of patients undergoing PrePex circumcision with same personal hygiene and with different foreskin hygiene techniques.

**Secondary Objectives**

- To determine an absolute odor level per each arm
- To determine a penis cleaning procedure guidelines safety and efficacy
- To compare the different perception of the subject’s partner relating to the odor when examine 3 arms of patients undergoing PrePex circumcision with same personal hygiene and with different foreskin hygiene techniques.

**Eligibility Criteria:**

**Inclusion Criteria:**

- Ages – 21 to 49 years
- Subject wants to be circumcised
- Uncircumcised
- Able to understand the study procedures and requirements
- Agrees to participate in either arm and to follow hygiene instructions
- Agrees to have Independent blinded smell reviewers in the same room on Removal visit
- Agrees that his partner will be interviewed via telephone
- Agrees to abstain sexual intercourse for 6 weeks post device removal
- Agrees to abstain from masturbation for 2 weeks post device removal
- Agrees to return to the health care facility for follow-up visits (or as instructed) after his circumcision for a period of 1 week
- Subject able to comprehend and freely give informed consent for participation in this study and is considered by the investigator to have good compliance for the study
- Subject agrees to anonymous video and photographs of the procedure and follow up visits.

**Exclusion Criteria:**

- Active genital infection, anatomic abnormality or other condition, which in the opinion of the investigator prevents the subject from undergoing a circumcision
- Subject with the following diseases/conditions: phimosis, paraphimosis, warts under the prepuce, torn or tight frenulum, narrow prepuce, hypospadias, epispadias
- Known bleeding / coagulation abnormality, uncontrolled diabetes, by questionnaire
- Subject who have an abnormal penile anatomy or any penile diseases
- Subject that to the opinion of the investigator is not a good candidate
- Subject does not agree to anonymous video and photographs of the procedure and follow up visits.

**Study Site:** The study will take place at Rwanda Military Hospital.

**Study arms:**

The subjects will be randomized into 3 study arms, using a randomization table and sealed envelopes:

**Arm 1:** A control arm – subjects instructed to follow the current hygiene instructions of standard washing with soap and water during a daily shower. They will get a soap to take home and will be questioned daily to make sure they followed the cleaning instructions.

They might be requested to wash themselves at the hospital before the actual Removal visit starts.

**Arm 2:** subjects instructed to clean the foreskin with soapy water once a day using a syringe.

They will get a soap and required accessories to take back home and will be questioned daily to make sure they followed the instructions.

Subjects may be requested to wash themselves at the hospital before the actual Removal visit starts.

**Arm 3:** subjects instructed to clean the foreskin with diluted chlorhexidine (1%) once a day using a syringe. They will get chlorhexidine in tubes and required accessories to take back home and will be questioned daily to make sure they followed the instructions.

Subjects may be requested to wash themselves at the hospital before the actual Removal visit starts.

**Independent Blinded Reviewers (herein: Smellers):**

3 smellers will be chosen to participate in the study to perform a smell test using smell detector device; the "Nasal ranger" device, see the following link for technical information:

[http://www.nasalranger.com/Operations/Nasal%20Ranger%20Operations%20Manual%20v6.2.pdf](http://www.nasalranger.com/Operations/Nasal Ranger Operations Manual v6.2.pdf)

The Smellers will go through a short training in order to know how to operate the device and to assess their skills.

On day 0 pre procedure, the smellers will use the Nasal Ranger device to smell each of the 100 subject's genitals (baseline). Below are the room and procedure requirements. Only after the smelling procedure, will the subject undergo PrePex procedure.

The subjects will arrive to the clinic on days 3, 5 and 7 in order to document their odor levels.

On the Removal day (Day 7), the smellers will attend the Removal procedures and use the Nasal Ranger device. Below are the room and procedure requirements:

- 2 rooms will be used during the study which will have the same constant conditions (same room with no initial smell, same window, same distance from the penis: 30 cm)
- Usage of Nasal ranger device by trained personnel only
- The subjects will be randomized for their turn to enter the room
- When the smeller enters the room, the subject face will be covered and he will not wear his clothes but hospital garment
- After all 100 subjects were smelled by all 3 smellers, the subjects will be randomized again for their turn to enter the room (new randomization)
- When the smeller enters the room, the subject face will be covered and he will not wear his clothes but hospital garment
- The room should be aired between subjects
- The smelling will be always in the same distance from the genitals, by measuring with a ruler, 30 cm distance between the genitals and the end of the "Nasal Ranger"
- Each Smeller will be asked separately to grade the smell as he performs it as it is shown in the "Nasal ranger"
- Only at the end of the smelling procedure will the foreskin and device be removed.

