***Statistical Analysis:***

All data will be presented via descriptive statistics. Binary data such as adverse events success/fail criteria will be presented as a count and percentage together with an exact 95% confidence interval. Adverse event rates will be compared descriptively with the reported rates of similar treatments. Continuous data will be represented by a mean, standard deviation, median, minimum and maximum together with 95% confidence intervals for the means.

Study Flow

Screen 120 candidates

100 enrolled subjects

Randomization

Arm 1 -33 subjects

- Standard PrePex
- General hygiene instructions
- Foreskin hygiene general instructions – daily shower

Arm 2 -33 subjects

- Standard PrePex
- General hygiene instructions
- Foreskin specific hygiene instructions – daily soapy water with syringe
- **Follow up visits days 3, 5 & 7**
- Subject questionnaires
- Odor tests by 3 Blinded smellers
- Partner questionnaire – on days 3, 5 & 7
- Removal on day 7
- A random sample of subjects were evaluated a second time on day 7
- Safety - AEs

Arm 3 – 33 subjects

- Standard PrePex
- General hygiene instructions
- Foreskin specific hygiene instructions - daily chlorhexidine with syringe

|  | **Randomization & Screening Visit** | **Applying Visit** |  |  | **Removal Visit** |
| --- | --- | --- | --- | --- | --- |
| **Visit #** | **1** | **2** | **3** | **4** | **5** |
| **Day (D)/week (w)** | **–7 to D0** | **D0** | **D3** | **D5** | **D7** |
| Informed consent | X |  |  |  |  |
| Randomization | X |  |  |  |  |
| Inclusion/exclusion criteria | X |  |  |  |  |
| Medical history & Demography | X |  |  |  |  |
| Current medication including pain killers | X | X |  |  | X |
| Genital examination and potential pictures | X | X | X | X | X |
| Device apply |  | X |  |  |  |
| Foreskin Removal |  |  |  |  | X |
| Device Removal |  |  |  |  | X |
| Subject's subjective pain, tingling and discomfort evaluation |  | X | X | X | X |
| Expected Side effects and AE |  | X | X | X | X |
| Smellers test |  | X | X | X | X |
| Questionnaires for patients & for sub group female partners (between days 5-6) |  |  | X | X | X |
| Statistical analysis of data |  |  |  |  |  |

Table of Contents

[Study Synopsis 2](#__RefHeading___Toc344626056)

[Schedule of Events 8](#__RefHeading___Toc344626057)

[1. Clinical background 12](#__RefHeading___Toc344626058)

[2. STUDY OBJECTIVES AND PURPOSE 15](#__RefHeading___Toc344626059)

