**If subject is unable to comprehend and sign the Consent Form, subject must not be enrolled in the study.**

## 6.3 Study Schedule of Events

The following represents the study schedule of events

1. The procedure will be performed in Rwanda Military Hospital
2. **Inclusion Exclusion Criteria** – Subjects will be evaluated for inclusion in the study according to inclusion and exclusion criteria. Subject which do not meet the criteria will be offered circumcision out of the study procedures and records
3. **Informed Consent** – Potential candidate for enrollment to the study will be consented
4. **Randomization -** Subjects who meet all of the inclusion exclusion criteria will be randomly assigned to one of the study arms – Arm 1, Arm 2 or Arm 3

**Note -** The PrePex Operators and Assistants must be formally trained with the most up to date training program and certified as PrePex Operator and Assistants in a formal PrePex training program to take place in Kigali, Rwanda. In addition there may be training refreshment during the procedure of the first 20 procedures of the study.

1. **Circumcision** -

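### The odor reading called baseline is taken at D0, after open-label randomization at Visit 1, so it could be influenced by knowledge of the arm

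*Protocol*

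**What the plan says.** In the Synopsis schedule of events, the first two columns are headed "Randomization & Screening Visit | Applying Visit" and the day row runs "7 to D0 | D0 | D3 | D5 | D7", with the first window opening at day -7. The randomization row has a single mark, in the first column: "Randomization | X". The smell-test row leaves that column empty and starts at Visit 2: "Smellers test | | X | X | X | X".

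The Synopsis section on the blinded smellers labels the D0 reading as the baseline: "On day 0 pre procedure, the smellers will use the Nasal Ranger device to smell each of the 100 subject's genitals (baseline". It orders this reading before device placement and says nothing about its order relative to allocation.

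Section 6.3 lists eligibility, consent, randomization and then circumcision, and states "Subjects who meet all of the inclusion exclusion criteria will be randomly assigned to one of the study arms". The method of allocation is in the Synopsis under Study arms: "The subjects will be randomized into 3 study arms, using a randomization table and sealed envelopes". No section says when the envelope is opened. The title, repeated in Sections 2.1 and 8.1, describes the trial as open label with blinded assessors.

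**The concern.** A baseline is useful because allocation cannot have affected it. Here the man may know his arm for up to a week before the reading is taken, and what is being tested is how he washes. The protocol's own premise (Synopsis and Section 1) is that odor depends on personal hygiene and washing technique. A man told that he is in a foreskin-cleaning arm, or in the arm that keeps the current instructions, may change his washing before D0. He also knows that his odor will be assessed. Blinding the smellers gives no protection, because the change would be in the odor itself.

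If that happened to different degrees in different arms, D0 odor would be partly a result of allocation. Subtracting it or adjusting for it would then remove part of the arm effect or create a spurious one, and a comparison of arms at baseline could show an imbalance that is not due to chance. No other odor reading precedes the device, so no clean baseline could be recovered at analysis.

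**Working it through.** **Order of events, from the schedule**

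- Randomization: Visit 1, day -7 to D0, and at no other visit.
- First smell test: Visit 2, D0. None at Visit 1.
- Gap: shortest 0 - 0 = 0 days; longest 0 - (-7) = 7 days, equal to the 7 days that the device is worn.
- Provision to withhold the arm, instructions or kit until the D0 reading: none found in the Synopsis, Section 6.3 or Section 8.2.

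So the reading follows randomization in the schedule. Where both fall on D0, the protocol does not say which comes first.

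**The plan's own sample size**

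Section 8.3 gives d = 0.7, 80% power and a 5% level; Section 8.3.1 makes tests two-sided. By the normal formula, n = 2(1.960 + 0.842)² / 0.7² = 15.70 / 0.49 = 32.04, rounded up to 33. The exact t calculation gives 33.02, with power 79.97% at 33. The stated 33 per arm is reproduced and does not depend on when the baseline is read.

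**What contamination would do, if it occurred**

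The inputs below are assumptions; none is in the documents. Washing before D0 lowers D0 odor by s SD in one cleaning arm only. It does not carry over to day 7. The true day 7 difference is 0.7 SD, there are 33 men per arm, and the D0 to day 7 correlation is ρ, with equal SDs.

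- Day 7 alone: expected difference 0.7, whatever s is.
- Change from D0: expected difference 0.7 - s, SD √(2(1 - ρ)).
- Adjusted for D0: expected difference 0.7 - ρs, residual SD √(1 - ρ²).

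With ρ = 0.5 the SDs are 1 and 0.866:

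| s | Change: effect | Change: power | Adjusted: effect | Adjusted: power |
|---|---|---|---|---|
| 0 | 0.70 | 80% | 0.70 | 90% |
| 0.1 | 0.60 | 67% | 0.65 | 85% |
| 0.2 | 0.50 | 52% | 0.60 | 79% |
| 0.3 | 0.40 | 36% | 0.55 | 72% |

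With ρ = 0.3, adjusted power is 80.2%, 76.6% and 72.5% for the three shifts, against 83.5% with a clean baseline. As a share of the target, the change-score loss is 0.1/0.7 = 14% to 0.3/0.7 = 43%. The adjusted loss at ρ = 0.5 is half of that, 0.05 to 0.15 SD.

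The sign can reverse: if control men changed their washing more, the contrast would be overstated. An equal shift in all arms would leave the contrasts unbiased.

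**The case against.** The strongest reply is that the protocol gives the D0 reading no stated role in the analysis. The sample size rests on a between-group t-test. The repeated measures ANOVA that replaces it is justified by the three smellers and three groups. The primary endpoint compares odor levels between arms, and the hypothesis in the Synopsis and Section 1 concerns odor on day 7. Section 8.3.3 tabulates baseline demographics and patient characteristics without mentioning D0 odor. This stands. A reader might infer that the primary comparison is biased; the documents do not support that, because no analysis using D0 is laid down and a day 7 comparison without it would not carry this bias.

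A reader might also infer that men do clean by arm before D0. The text points the other way: the washing hypothesis is about men wearing the device, a discharge session follows placement, and the subject questionnaire, which covers compliance, first appears at D3. No section has kits issued before D0. What remains is a spontaneous change of habit by a man who knows his arm, which is possible but not shown.

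Two further points also stand. Arm 1 men are told to wash daily and are given soap too, so washing could rise in every arm, and only a difference between arms matters. And the feared odor comes from necrotizing tissue that does not exist before placement.

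None of this removes the sequence. The protocol calls the reading a baseline and schedules it after open allocation. That is a matter of trial conduct fixed by the protocol, and an analysis plan could not undo it.

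**Conclusion.** The point holds as a weakness in the order of events. The only pre-device odor reading is a post-randomization measurement, taken 0 to 7 days after allocation in an open-label trial of a self-performed behaviour, with no safeguard on disclosure of the arm. It could be affected by knowledge of the arm; whether it would be is not shown.

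Any bias depends on two conditions: D0 odor is used as a baseline, and washing before D0 shifts differently between arms. The size is unknown from the documents. The 14% to 43% range and the power figures follow only from assumed shifts of 0.1 to 0.3 SD and, for power, an assumed correlation; they should not be read as estimates of bias in this trial. The sample size is unaffected. This is a modest design point, worth correcting because the correction is cheap and the reading cannot be repaired later.

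**What to change.** Move the randomization mark in the schedule of events from Visit 1 to Visit 2 (D0) and retitle Visit 1 as a screening visit. Consent, eligibility and history stay at Visit 1. State in Section 6.3, and in the Synopsis section on the smellers, that each man's sealed envelope is opened, and his arm-specific instructions and kit given, only after all three smellers have recorded his D0 reading.

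The cost is an edit to the schedule and one instruction to the site. Placement already takes place on D0, so there is no extra visit, and 33 per arm is unchanged. The small downside is that kits for every arm must be ready on D0.

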## 8.3 Statistical analysis

**Sample size:**

The intention is to obtain at least 100 evaluable subjects under Rwanda ethical responsibility (RNEC), determining to use the most deducted calculation setting and to maintain allocation ratio of 1:1:1 between the 3 study arms (33 per arm).

A sample size for the study was determined based on the two-sample t-test. In order to detect an effect size of 0.7 (Cohen's D) with 80% and at and a 5% level of significance between any two groups a sample size of 33 subjects is required. In the study each subject will have a smell test repeated by three different smellers this will be in order to examine the variability in odor sensation between different clinicians. Given this design and the three groups that will be compared, a statistically more powerful model (repeated measures ANOVA) is used instead of a t-test, and thus the study will be appropriately powered.

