## 8.3.1 General Considerations

The primary analysis will be performed on an intent-to-treat basis. Per-protocol analysis also will be performed as a secondary analysis. The required significance level of findings will be equal to or lower than 5%. All statistical tests will be two-sided. Where confidence limits are appropriate, the confidence level will be 95%.

All data will be presented via descriptive statistics. Binary data such as adverse events success/fail criteria will be presented as a count and percentage together with an exact 95% confidence interval. Adverse event rates will be compared descriptively with the reported rates of similar treatments. Continuous data will be represented by a mean, standard deviation, median, minimum and maximum together with 95% confidence intervals for the means.

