## 8.3.3 Primary Endpoint Analysis

Baseline demographics and patient characteristics will be presented in tabular format. The statistical evaluation of baseline characteristics will include all available data from the ITT population.

The analysis of odor levels will include database which will analyze the correlation between odor levels, subjects and subjects' partners questionnaire results.

The primary end-point evaluations will be performed based on both the ITT and the per-protocol populations.

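### Day-0 odor is measured in every subject, but the protocol does not say how it enters the arm comparison; it should be a covariate, not an outcome time point

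*Protocol*

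**What the plan says.** The Synopsis section on the independent blinded reviewers sets the day-0 measurement: "On day 0 pre procedure, the smellers will use the Nasal Ranger device to smell each of the 100" subjects' genitals, and labels it baseline. The schedule table in the Synopsis puts the smellers' test at D0, D3, D5 and D7.

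The sample-size text, given both in the Synopsis and in section 8.3, has no covariate: "A sample size for the study was determined based on the two-sample t-test". The same paragraph then says that, because three smellers repeat the test and three groups are compared, "a statistically more powerful model (repeated measures ANOVA) is used instead of a t-test", and it concludes that the study is adequately powered. It lists no factors, time points or covariates for that model.

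Section 3 defines the primary endpoint as odor levels across the three arms, without a visit or a reference to baseline. Section 8.3.3 covers the tabulation of demographics and patient characteristics, where "The statistical evaluation of baseline characteristics will include all available data from the ITT population", and the correlation of odor with the questionnaires. Neither section mentions day-0 odor.

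**The concern.** The trial records a pre-placement value of its own primary outcome, with the same smellers and device as later, and then does not say what it is for. Two consequences are possible.

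If day 0 is left out, any part of the between-subject variation that it predicts stays in the error term, in a design with no reserve over 80% power for a single pairwise comparison.

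If day 0 goes into the repeated measures ANOVA as one of four visits, the arm main effect is averaged over a visit at which the arms cannot differ because of treatment. That dilutes the effect.

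The sample-size paragraph rests its power claim on the named model being more powerful than a t-test, so it matters which model is meant.

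**Working it through.** **Inputs from the Protocol (section 8.3, Sample size; section 8.3.1)**
- Effect: "In order to detect an effect size of 0.7" (Cohen's d). No raw difference or SD is given.
- Power and level: "with 80% and at and a 5% level of significance"; I read the 80% as power.
- Sidedness: "All statistical tests will be two-sided".
- Size: 33 per arm, allocation 1:1:1.

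**Step 1. Reproduce the plan's figure.** For a two-sample t-test with d = 0.7 and two-sided 5%, the normal approximation gives n = 33 per arm. The exact noncentral-t solution is 33.02. Power at 33 per arm is 81.2% (normal) or 80.0% (t). The stated figure reproduces. A one-sided test would need 26, so the calculation is two-sided.

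**Step 2. Add day 0 as a covariate.** Let r be the correlation between day-0 and follow-up odor. The residual variance is multiplied by 1 − r², so the effective standardized difference is 0.7/√(1 − r²). The Protocol gives no r, so it is an assumption shown over a range.

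| r | variance removed (r²) | effective d | power at 33 per arm (t) |
|---|---|---|---|
| 0 | 0% | 0.700 | 80.0% |
| 0.1 | 1% | 0.704 | 80.4% |
| 0.2 | 4% | 0.714 | 81.5% |
| 0.3 | 9% | 0.734 | 83.5% |
| 0.5 | 25% | 0.808 | 89.9% |

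Taking off one degree of freedom for the covariate changes these powers by less than 0.1 percentage point.

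**Step 3. A change score is not a substitute.** With equal SDs its variance is 2(1 − r) times that of a single reading. At r = 0.2 this is 1.6, and power is 60.0%. At r = 0.3 it is 1.4, and power is 65.8%. It only breaks even at r = 0.5, where the factor is 1.0 and power is 80.0%.

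**Step 4. Day 0 as an outcome level.** Illustration only. Assume a constant 0.7 SD effect on days 3, 5 and 7, equal SDs, and the same correlation ρ between all visits.
- Mean of the three post-baseline visits: effect 0.7, variance (1 + 2ρ)/3.
- Mean of all four visits: effect 0.7 × 3/4 = 0.525, variance (1 + 3ρ)/4.
- Mean of the three visits with day 0 as covariate: effect 0.7, variance (1 + 2ρ)/3 − ρ².

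| ρ | three visits, day 0 unused | four visits, day 0 as a level | three visits, day 0 as covariate |
|---|---|---|---|
| 0.3 | variance 0.533, power 97% | variance 0.475, power 86% | variance 0.443, power 99% |
| 0.5 | variance 0.667, power 93% | variance 0.625, power 76% | variance 0.417, power 99% |

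The absolute powers depend on the constant-effect assumption. The ordering is the point: under these assumptions, treating day 0 as an outcome level does worse than ignoring it.

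**The case against.** The strongest objection is that the Protocol is only silent. It never says that day 0 is excluded, and the repeated measures ANOVA is named in a sample-size paragraph without terms. Covariates are commonly left to a statistical analysis plan, which is not at hand. A reader might infer that the baseline reading is discarded, but the text does not support that. Day 0 could be a covariate, a repeated level or unused. What survives is that the Protocol names a model, describes its repeats only as smellers and draws its power claim from it, so specifying that model here is reasonable.

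A reader might also take section 8.3.3 to mean that baseline odor is merely tabulated. That sentence concerns demographics and patient characteristics. It does not mention odor and does not restrict baseline data to tables.

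The benefit may be small. The background section attributes the odor of concern to the necrotizing foreskin, whereas day 0 precedes placement. The source of the odor differs, so r may be near zero; at r up to 0.2 the gain is under 2 percentage points. This stands, and it limits the claim. Chance imbalance at baseline is likewise noise under randomization, not bias.

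Finally, randomization is scheduled at visit 1 (day −7 to day 0), the trial is open label, and the Protocol does not say when subjects receive their arm's cleaning instructions. The reading precedes placement and is made by blinded smellers, but it may follow knowledge of allocation. That is worth confirming and does not defeat the proposal.

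**Conclusion.** The point holds as an efficiency and clarity matter. Every subject has a pre-placement odor reading called baseline, and the Protocol gives it no role in the comparison of arms. Used as a covariate at 33 per arm and d = 0.7, it would raise power from 80.0% to somewhere between 80.4% (r = 0.1) and 89.9% (r = 0.5). This rests on an assumed r, equal SDs and a single pairwise comparison at two-sided 5%. With r near zero, almost nothing is gained and almost nothing lost. The clearer benefit is to rule out entering day 0 as an outcome level.

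It would be tempting to conclude that the trial is undersized or the analysis invalid. Neither follows: the 33 per arm reproduces, and an unadjusted randomized comparison is valid.

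**What to change.** In the sample-size text of the Synopsis and of section 8.3, replace the unspecified repeated measures ANOVA, and add the model to section 8.3.3, which at present names none. State that:
- post-baseline odor readings are compared between arms with a linear mixed model, with subject as a random effect and smeller, arm and day as terms;
- the subject's day-0 odor, averaged over the three smellers, is a covariate;
- day 0 is not an outcome time point, and no simple change from baseline is used.

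Also state whether the day-0 reading comes before subjects receive their arm's cleaning instructions.

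The cost is wording and one degree of freedom. No extra subjects or measurements are needed, and the sample size can stay as it is. The choice should be fixed before outcome data are seen by arm, so that unadjusted, change-score and adjusted results are not chosen among afterwards.

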3. STUDY ENDPOINTS

**Endpoints:**

**Primary Endpoint:**

- The primary endpoint is to assess the different odor levels by evaluating 3 arms of patients with different foreskin hygiene techniques.

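### The cleaning product differs by arm and the time from last cleaning to smell test is not controlled, so product scent or recent washing, if detectable, could shift the single smell grade in either direction and make Arm 3 recognisable

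*Protocol*

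**What the plan says.** The Study Synopsis and section 1 (Clinical background) give the motive as "the potential of strong odor extraction from the necrotizing foreskin". Section 3 states the endpoint: "The primary endpoint is to assess the different odor levels by evaluating 3 arms of patients with different foreskin hygiene techniques".

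The Synopsis, under Independent Blinded Reviewers, describes the reading: "Each Smeller will be asked separately to grade the smell as he performs it". The grade is the one shown on the Nasal Ranger, held at a measured 30 cm. Readings are taken on day 0 before placement and again on D3, D5 and D7.

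The Synopsis (Study arms) and section 8.2 define the arms by product and delivery:
- Arm 1: "standard washing with soap and water during a daily shower"
- Arm 2: "subjects instructed to clean the foreskin with soapy water once a day using a syringe"
- Arm 3: "subjects instructed to clean the foreskin with diluted chlorhexidine (1%) once a day using a syringe"

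Each arm description adds that subjects might or may be asked to wash at the hospital before the Removal visit. Neither place says who is asked, with what product, or how long before the test. Home cleaning is daily with no stated hour, and no interval to the D3, D5 or D7 reading is given.

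The smeller is masked by a covered face and a hospital garment. The order of entry is random, the rooms have no initial smell, and they are aired between subjects.

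**The concern.** The motive is odor from the dying foreskin, but the grade covers everything the smeller detects at 30 cm. Two things that differ, or may differ, by arm can enter that grade: the scent of the cleaning product, and how recently the subject washed. The protocol fixes neither at the time of the reading.

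Two consequences follow if a product is detectable then. First, the contrast between arms may partly reflect product or timing. Added scent could hide a benefit, while scent that covers foul odor, or a wash just before the test, could create or enlarge one. Second, the design relies on a blinded assessor because treatment is open label. The covered face and garment protect against sight, not smell, and Arm 3 is the only arm whose syringe product is an antiseptic.

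This cannot be left to the analysis. If time since cleaning and odor character are not recorded at the visit, no model can recover them.

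**Working it through.** **1. What each safeguard covers.**
- Covered face and garment: sight and identity.
- Random order of entry: order effects.
- Rooms without initial smell, aired between subjects: carry-over between subjects.
- Day 0 reading: smell before the device is placed. It precedes the assigned cleaning, so it cannot remove scent that arises from that cleaning afterwards.
- Three smellers: a subject's mean grade is foreskin odor + shift + average smeller error. Averaging shrinks only the last term. A shift that all three smellers meet stays whole, and more subjects do not remove it.

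None of these equalises product scent or time since washing.

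**2. Which arms product scent could identify.** Arms 1 and 2 both use soap, so recognising soap does not tell them apart. Between them only delivery and any residue differ. A product cue could separate Arm 3 from the other two.

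**3. The plan's own sample size.** Inputs from section 8.3: d = 0.7, power 80%, 5% level, 33 per arm. Section 8.3.1: two-sided tests.

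Normal approximation: n = 2 × ((1.96 + 0.8416) / 0.7)² = 32.04, rounded up to 33.

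Exact two-sample t-test (noncentral t, 2 × 33 − 2 = 64 degrees of freedom, noncentrality d × √(n/2) = 0.7 × √16.5 = 2.84): power 79.97%. The stated 33 per arm reproduces.

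**4. What a shift would do.** Let b be the difference between two arms in mean grade, in SD units, that comes from product scent or time since washing alone. The documents give no value for b, so the range is an assumption. The same noncentral t is used with n = 33 per arm, replacing d by 0.7 − b (the shift offsets a true 0.7 SD benefit) or by b (no true difference).

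| Assumed b (SD) | Power when b offsets a true 0.7 SD | Chance of a significant pair with no true difference |
|---|---|---|
| 0 | 80.0% | 5.0% |
| 0.1 | 67.0% | 6.9% |
| 0.2 | 51.6% | 12.6% |
| 0.3 | 36.0% | 22.5% |
| 0.5 | 12.6% | 51.6% |

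If the shift instead adds to a true benefit, 0.7 SD would be seen as 0.7 + 0.1 = 0.8 up to 0.7 + 0.5 = 1.2 SD.

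The t-test is used because the plan sizes the trial on it. The planned repeated measures ANOVA would give different percentages, but it would carry the same shift.

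**The case against.** The strongest reply is that the premise is not in the document. Nothing says that the soap or the chlorhexidine can be smelled at 30 cm, hours after use or at all. That stands. The shift is an assumption, the table only translates it, and with odorless products the scent part is zero.

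Second, total smell may be the intended outcome. Section 3 links odor levels to acceptability, the title speaks of uptake, and subjects and partners judge smell as a whole. This also stands in part, since a total grade is relevant to acceptability. It does not answer the timing point: a grade taken soon after a wash and one taken many hours later are not the same measurement of total smell either.

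Third, the grade is tied to a device with a linked manual, and the smellers are trained. Instructions on odor character might sit in the manual, the training or the case report form, none of which is at hand. That limits what can be said about character. It does not supply the interval or the hospital-wash rule, which belong to the visit procedures described here.

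A reader might also infer that a smeller who recognises the product always knows the arm, so that blinding fails throughout. The protocol does not support this, because Arms 1 and 2 share soap. At most Arm 3 is exposed, and only if its product can be smelled.

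**Conclusion.** The point holds as a conditional weakness in how the primary outcome is measured. The text establishes one total grade, products that differ by arm, no cleaning-to-test interval, a discretionary wash before the Removal visit, and masking that does not reach the sense being used.

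Two further inferences are tempting and go too far. One is that the primary contrast is biased. The documents show only that it could be, in either direction and by an unknown amount. The other is that the trial loses power. Power loss is one possible result, and inflated false positives or an overstated benefit are equally possible.

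On the assumed range, pairwise power would fall from 80% to 67% at 0.1 SD and 13% at 0.5 SD if the shift opposes a true 0.7 SD benefit. With no true difference, 0.2 to 0.3 SD would raise pairwise false positives from 5% to about 13% to 23%. The sample size itself is correct and needs no change.

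The change should be made because it is nearly free and the missing information cannot be recovered later.

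**What to change.** In the Synopsis (Study arms and Independent Blinded Reviewers) and section 8.2:

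1. Set one interval from last cleaning to smell test, the same in all arms and at D3, D5 and D7, and record the clock time of the last cleaning and of the test. The length is for the sponsor and investigator to choose.
2. Replace the discretionary hospital wash with a single rule for every subject, either all or none, with the same timing relative to the smell test. Which of the two is again their decision. Without this, the day 7 interval can be broken even if home cleaning is timed.
3. After the grade is written down, have each smeller record odor character (foul, product, neutral), and report it by arm. This would show whether product scent was present at all.

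If a check of the blind is wanted, ask for the arm guess only after the last reading. The same three smellers grade the subjects repeatedly, and a guess after each grade would prompt them to infer allocation. Using the same low-scent soap wherever soap is supplied is optional, because Arm 1 is defined by current hygiene instructions and a change of soap could alter the control.

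The cost is less scheduling freedom at the visits and one extra item on the smeller form.
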